#### 7.4 Benefits to Participants

This study has some minimal risks associated with participation and we anticipate that few participants will experience negative events as a result of taking part in the study. This research will improve our understanding of how an adapted and enhanced FB may improve depression and engagement in HIV care among ALWH. Long-term, supporting ALWH with depression through a counseling intervention carried out by counselors is expected to reduce depression, improve engagement in HIV-care, and ultimately improve adolescent health and HIV outcomes. Therefore, the risk to individual participants in our study is small and the potential benefit to society is substantial.

## 7.5 Costs and Compensation

Study participants will receive standard compensation in line with UNC Project Malawi practices for their enrollment visit and research outcome interviews.

## 7.6 Informed Consent

In this study, we are seeking to enroll adolescents 13-19 years to participate. Adolescents who are 18 years or older will provide consent for themselves. Adolescents 13-17 years will provide assent and will have an authorized adult over 18 years provide consent for them prior to participation. The authorized adult can be a parent, a legal guardian, or someone designated as an authorized representative. The research study will be described briefly to all adolescents accessing ART services at Area 18, Area 25, Kawale, or Lighthouse Health Centers in Lilongwe while they wait in the reception area. Once a participant is determined to be eligible for the study a research assistant will complete an informed consent process with each participant in their native language, Chichewa. During the informed consent process, the research assistant will describe the procedures to be followed, the risks and benefits of participation, the duration of participation, and the steps taken to protect participant's confidentiality, particularly with respect to keeping all personal and private information (such as HIV and depression status) private to the extent possible by the study team. The counselor will also emphasize that the consent form says that confidentiality of sensitive information cannot be assured during peer support sessions. Illiterate participants may sign the consent form via thumbprint, in the presence of an impartial witness. Any questions or concerns about privacy will be answered by the study coordinator or referred to the PI, who will address them. To provide protection to this group, we will have rigorous trainings of research staff. We will teach staff to be sure that there is an adequate assessment of understanding. Staff will ensure participants fully understand the content, and time for questions will be encouraged, and answered honestly. We will be clear that refusals will not compromise access to services in any way. We will follow a work practice guideline of when mandatory reporting is required and the best methods to do so, e.g. evidence of exploitation or sexual abuse. Additionally, both sites will adequately map out referrals services to deal with a range of potential needs. All ALWH who screen positive for depression but are not interested in the study will be referred to outpatient psychiatry services. Written informed consent will be obtained from each participant and participants will be provided with a copy of their informed consent forms if they are willing to receive it. Study staff will document the informed consent process.

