**6.2 Place of Study:** The participating health centers will be the Area 18, Area 25, Kawale, and Lighthouse Health Centers. These sites are all government health facilities located in urban Lilongwe, Malawi with ART clinics on their grounds. We selected clinics well matched in terms of staffing levels, services offered, NGO/ancillary program involvement (e.g., all three sites receive training and supervision support from the Lighthouse Trust NGO in Lilongwe), patient volume, and patient population to minimize any important differences between the sites. UNC-Project Malawi will serve as the administrative home for the study and has longstanding relationships with all 4 proposed study sites. UNC Project-Malawi has previously successfully recruited and enrolled adolescents in several sexual and reproductive health studies as well as HIV-related clinical trials.

**6.3 Target Population: ALWH:** We will recruit 105 ALWH from 4 HIV clinics in Lilongwe, Malawi. We aim to recruit for diversity in age, gender identity, and HIV acquisition type. ALWH will be eligible for the study if they are: (1) age 13-19; (2) diagnosed with HIV; (3) scored  $\geq 13$  on the self-reported BDI-II; (4) willing to provide consent (age 18 or 16-17 years old and married (emancipated minors per Malawi law) or assent with parental consent (age 13-17). All HIV+ individuals will be eligible for recruitment including ART initiators, ART re-initiators and established patients. ALWH screening positive for depression who choose not to participate will be referred to a mental health provider.

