## 7.0 ETHICAL CONSIDERATIONS

### 7.1 Human Subjects

Safety considerations. Study staff will evaluate patients for safety who endorse any level of suicidal ideation whether or not they enroll in the study. Safety assessment results will be conveyed to the clinical team as appropriate for further follow-up according to the clinic's standard operating procedures.

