- (4) If the participant is not actively in distress, then the study investigators, project manager, and other appropriate project supervisory staff will develop a plan for referring the participant to the clinic lead. As appropriate, the project team may consult the clinic lead in developing the plan. (All consent forms will note that investigators may need to break confidentiality when there is a threat of harm to self or others.) The timing and most appropriate means of effecting a referral will be dependent on the nature of the problem. For example, if a participant reports child abuse in the home, then it would be necessary to involve appropriate social services to investigate the problem. By contrast, if a participant reports that she/he is facing ongoing (but not life threatening) emotional abuse from a partner, then it may make more sense for the navigator to first approach the participant and encourage her/him to meet with a clinic provider or with other social support services in the area.
- (5) Study investigators will inform all governing IRBs of the incident and update the IRBs as necessary on the outcomes of efforts to intercede and resolve the harm.

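### Section 7.6 starts consent only after eligibility is determined, so as written adolescents, including minors, complete the BDI-II before assent, guardian consent or the warning that confidentiality may be broken.

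*Protocol*

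**What the plan says.** Section 7.6 describes two steps. The study is first described briefly to adolescents in the clinic reception area. Then: "Once a participant is determined to be eligible for the study a research assistant will complete an informed consent process with each participant".

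Section 6.3 lists the eligibility criteria. The third is a score of at least 13 "on the self-reported BDI-II".

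Two sections provide for adolescents whose depression status is known before they decide about the study. Section 6.3 says "ALWH screening positive for depression who choose not to participate will be referred to a mental health provider". Section 7.6 says "All ALWH who screen positive for depression but are not interested in the study will be referred to outpatient psychiatry services".

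Section 7.1 adds: "Study staff will evaluate patients for safety who endorse any level of suicidal ideation whether or not they enroll in the study".

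On minors, section 7.6 says: "Adolescents 13-17 years will provide assent and will have an authorized adult over 18 years provide consent for them prior to participation".

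On the limits of confidentiality, section 7.3 says: "All consent forms will note that investigators may need to break confidentiality when there is a threat of harm to self or others". Section 7.3 also promises in general terms that discomfort from surveys will be reduced by telling participants in advance what the interaction involves and by holding it in private.

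**The concern.** The BDI-II is a depression questionnaire, and some of those who answer it are 13 to 17 years old. If consent begins only once eligibility is known, the answers come before the adolescent has assented and before an adult has agreed.

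The order also works against the protocol's own safeguard. The warning that confidentiality may have to be broken is useful only if it is heard before a disclosure. Here it sits in the consent forms, which are reached after the screen. An adolescent can disclose suicidal ideation, and so bring about the 7.1 evaluation, without having heard it. One who screens negative never reaches the form at all.

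What is at stake is the protection of people who are screened, most of whom will not enroll. No estimate, comparison or sample size is affected.

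**Working it through.** The point is procedural, and the plan states no figure that could be reproduced. The check has two parts: the order of steps, and the number of people it touches.

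**Order of steps**

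1. Consent follows the determination of eligibility (7.6).
2. Eligibility requires a BDI-II score of at least 13 (6.3), so the BDI-II comes before consent.
3. Sections 6.3 and 7.6 both refer adolescents who screen positive and then decline. Their depression status is known before they decide, which confirms step 2.
4. Section 7.1 expects some people who never enroll to endorse suicidal ideation. The protocol does not say that the BDI-II itself asks about this, so the possibility of disclosure rests on 7.1.
5. The confidentiality warning is placed in the consent forms (7.3), so it comes after the screen.
6. The steps described ahead of the screen are the brief description in the reception area (7.6) and the general promise of advance information (7.3). Neither is a screening agreement. The protocol body mentions no assent, guardian permission or waiver for screening, and the budget (10.1) pays guardian travel for the enrollment visit only.

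**Scale**

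Inputs:
- enrollment target 105 (6.3)
- depression prevalence 18%, the planning value (6.3), up to 26% (2.1)
- participation rate 80% (6.3)

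Assumptions: the prevalence equals the share scoring at least 13 on the BDI-II, and refusal comes after screening.

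Number who must screen positive = 105 / 0.80 = 131.25, of whom 131.25 - 105 = about 26 reach consent and decline.

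Number screened = 105 / (prevalence × 0.80):
- at 18%: 105 / 0.144 = 729; not enrolled 729 - 105 = 624
- at 26%: 105 / 0.208 = 505; not enrolled 505 - 105 = 400

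Taking out the 26 who decline, about 598 (at 18%) or 374 (at 26%) screen negative and never reach the consent step.

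Section 6.3 does not say where the 80% applies. If refusal comes before screening, number screened = 105 / prevalence:
- at 18%: 105 / 0.18 = 583; not enrolled 583 - 105 = 478
- at 26%: 105 / 0.26 = 404; not enrolled 404 - 105 = 299

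These counts cover all adolescents aged 13-19. The share aged 13-17, for whom 7.6 requires guardian consent, is not given.

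**The case against.** The strongest reply is that this rests partly on what the protocol does not say. The consent forms are not in the text available for review, 7.3 speaks of consent forms in the plural, and 7.2 sends all protocol materials to two ethics bodies before any data are collected. A screening form or an approved waiver could exist. Section 7.6 also requires assent and adult consent before participation, and 7.3 promises advance information and the right to refuse any question.

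Part of this stands. A reader might infer that minors will in fact be screened with no agreement of any kind. The documents do not support that; they show what the protocol body prescribes. But the order is stated, not merely left open. The requirement about participation does not repair it, because the protocol never says that screening counts as participation. General information given beforehand is not assent or guardian permission.

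Four further inferences are tempting and should not be drawn:

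- **That the BDI-II is proven to lie outside routine care.** Section 6.1 lists treatment and referral options for mental health. It does not say what the ART clinics screen for.
- **That the criteria are circular in a way that matters**, because the fourth is being "willing to provide consent (age 18 or 16-17 years old and married" and so on. This is a conventional item, met when consent is given, and it does not change when the BDI-II is completed.
- **That the feasibility outcome would be lost.** Section 6.7 asks for enrollment counts and reasons for non-enrollment, not the BDI-II answers of people who stay out. Nothing in the protocol makes those counts unusable.
- **That all 624 are minors who never see a consent form.** The figure covers ages 13-19 and includes about 26 who are offered consent and decline.

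**Conclusion.** The concern holds against the protocol as written. Sections 6.3 and 7.6 together put the BDI-II before assent, guardian consent and the confidentiality warning, and 6.3, 7.1 and 7.6 each provide for people who are screened or evaluated and never enroll.

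On the protocol's own planning values the order affects about 505-729 adolescents, or about 404-583 if refusal comes before screening. Both ranges assume that the 18%-26% prevalence applies at the BDI-II cut-off. How many are minors cannot be derived.

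This is a matter of participant protection that should be corrected. If a screening form or waiver already exists, the protocol needs only to say so and to place it before the BDI-II.

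**What to change.** In 7.6, ahead of the BDI-II, add a short screening step that:

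- obtains self-consent, or assent with guardian permission, or assent under an IRB-approved waiver of that permission
- explains the limits of confidentiality, including what happens when there is a risk of harm.

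Reword the sentence on consent along these lines: *Once screening agreement has been obtained and eligibility determined, full informed consent is completed.* Then reconcile 6.3, 7.1, 7.3 and 7.6 so that they describe one sequence. There is no need to extend the step to keeping screening answers for the feasibility analysis, which 6.7 does not call for.

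The cost is a short script, IRB review and a few minutes per adolescent. If no waiver is granted, minors who attend alone must be screened later, which would slow recruitment somewhat.

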
## 7.7 Adverse Event Reporting

We do not anticipate any adverse events occurring given the nature of the minimal risks associated with this research. However, in the case that a breach of confidentiality does occur, the study team will immediately inform the IRBs. Specifically:

- Deaths related to study participation shall be reported by the PI to the NIMH PO immediately and no later than within 5 business days of the PI first learning of the death
- SAEs related to study participation shall be reported by the PI to the NIMH PO within 10 business days of the study team becoming aware of the SAE
- Unanticipated Problems Involving Risks to Subjects or Others shall be reported by the PI to the NIMH PO within 10 business days of the study team becoming aware of the problem
- Adverse events and SAEs, including deaths, that are deemed expected and/or unrelated to the study shall be submitted in summary form to the NIMH PO with the annual progress report
- All reported social harms will be documented and communicated to NHSRC and UNC IRB in 7 days
- Protocol violations shall be submitted in summary form to the NIMH PO with the annual progress report
- Suspension or termination of study by IRB shall be reported by the PI to the NIMH program officer (PO) within 3 business days of receipt

## 7.8 Study Discontinuation

The study may be discontinued at any time by the UNC IRB, the NHSRC, or other government agencies as part of their duties to ensure that research participants are protected.

## 9.0 WORK PLAN

This pilot trial will be conducted over 18 months. Psychosocial Counselor and Peer Supporter trainings will be conducted in the first 4 months. The pilot trial will be conducted over 12 months, following regulatory approvals.

|                                                  | Months |   |   |   |   |   |   |   |   |    |    |    |    |    |    |    |    |    |
|--------------------------------------------------|--------|---|---|---|---|---|---|---|---|----|----|----|----|----|----|----|----|----|
|                                                  | 1      | 2 | 3 | 4 | 5 | 6 | 7 | 8 | 9 | 10 | 11 | 12 | 13 | 14 | 15 | 16 | 17 | 18 |
| Psychosocial Counselor & Peer Supporter Training |        |   |   |   |   |   |   |   |   |    |    |    |    |    |    |    |    |    |
| 3-Arm Pilot Implementation and Follow-up         |        |   |   |   |   |   |   |   |   |    |    |    |    |    |    |    |    |    |
| Pilot Results Analysis and Resulting Manuscript  |        |   |   |   |   |   |   |   |   |    |    |    |    |    |    |    |    |    |

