## 6.0 METHODOLOGY

6.1 Design of Study: We will conduct a three-arm individual-level clinical pilot trial across four clinics. Clinics will be randomized either to adapted Friendship Bench (N = 35 ALWH), enhanced friendship bench (N = 35 ALWH), or standard of care (N = 35 ALWH). Participants will all be recruited and followed for 12 months.

The Adapted Friendship Bench (AFB) will be adapted from the existing Friendship Bench intervention protocol to be youth-friendly and address the unique needs of ALWH. Youth friendly adaptation will include selection of young counselors (mixed genders, aged 20-35) who are motivated to work with young people. Counselors will be trained to deliver non-judgmental counseling that respects the privacy and autonomy of ALWH and enables them to make free and informed choices that are relevant to their individual needs. Training will also include discussion of adolescent development and the unique experiences of ALWH related to stigma, disclosure, social relationship issues, and health care access. Counseling sessions will take place in a youth oriented but discrete location within the HIV clinic and be available on weekends to ensure accessibility. AFB will include 6 individual counseling sessions facilitated by counselors attached to one of the study HIV clinics. The first session includes three components called Opening the Mind, Uplifting, and Strengthening, with subsequent sessions building on the first. Opening the Mind refers to the therapeutic process by which, through asking questions, clients are encouraged to open their minds to identify their problems, choose one to work on, identify a feasible solution, and agree on an action plan through an iterative process guided by the counselor. Each structured session lasts 30-45 minutes and will be conducted in a private clinic room in the participant's local language (Chichewa). No specific retention support will be provided, but participants may identify barriers to engagement in HIV care to address during their counseling session. After 4 sessions of individual therapy, the counselor can refer participants not improving or with suicidal ideation to a supervisor trained in mental health to reassess and manage the case. Case management may include additional counseling or pharmacotherapy, at the discretion of the managing clinician.

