Feasibility of ALWH Recruitment: The proposed study will be conducted at 4 comparable, public health centers in Lilongwe District, Malawi: Area 18, Area 25, Kawale, and Lighthouse. Each of the 4 health centers provides ART services, is located in the urban or peri-urban areas of Lilongwe on a main road, and has a monthly ART clinic volume > 115 individuals (age 10-19) who are either initiating care or established patients. We expect 90% will be between the ages of 13-19. Based on studies among ALWH in Malawi, we conservatively estimate 18% will have depression. Assuming an 80% participation rate, enrolling ~6 ALWH presenting with depression (age 13-19) per site per month (35 ALWH total per site) is feasible in 3 months for a total of 105 ALWH in the entire study. Though current government led data collection efforts for ART care in Malawi include adolescents aged 10-19 and our proposed study includes adolescents in a smaller age window (age 13-19), we believe that our conservative recruitment efforts account this mismatch.

Psychosocial Counselor Recruitment: We will recruit 3 young individuals to be psychosocial counselors at each clinic who will provide the 6 individual counseling sessions to participants (approximately 70 sessions per counselor over 4-6 months). Peer Supporter Recruitment: We will recruit 3 peer supporters for the Enhanced FB arm from the Community Advisory Board, Baylor Teen Club Graduates, and YFHS Clinic Experts. We will aim to select peer supporters who are varied in age, gender, and HIV acquisition status. Supervision for the peer supporters will be provided by the study coordinator.

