##### Primary Outcomes:

- Feasibility: will be defined as the ability to successfully enroll and retain depressed ALWH in the study. Feasibility will be assessed as the number of ALWH enrolled, a comparison of planned to actual enrollment and reasons for non-enrollment, and the proportion of ALWH retained in each arm by the end of the study period. We will also assess the number of sessions that participants attended and peer support engagement during the study period.
- Fidelity: will be defined as adherence to the intervention protocol. Fidelity to content for sessions will be assessed by a member of the research team using a checklist of intervention characteristics. Covering at least 80% of checklist items during each session will be considered fidelity to the intervention protocol.
- Acceptability: will be defined as the ability to deliver and participate in a useful intervention that is appropriate regarding resources and culture. Acceptability will be assessed through brief exit interviews with a sample of ALWH, all study staff, and supervisors. Exit interviews will assess how easy the intervention was to participate in or deliver, the perceived usefulness of the intervention, suggestions for improvement, and will explore contextual factors that impeded or facilitated implementation.

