#### 10.1 Budget Justification (USD)

##### Personnel

Two Research Assistants in Malawi (\$10,800 - 100% effort for 12.0 months) – Two research assistants in Malawi will be hired and trained to assist with the pilot trial. \$450 salary/month x 12 months x 2 research assistants = \$10,800

Total Personnel Costs \$ 10,800

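### The 12-month pilot window cannot hold 3 months of enrolment plus a 12-month visit for every participant; at least 15 months are needed

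*Protocol*

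**What the plan says.** Protocol Section 9.0 gives two durations for the same pilot. It opens with "This pilot trial will be conducted over 18 months", then adds "Psychosocial Counselor and Peer Supporter trainings will be conducted in the first 4 months" and "The pilot trial will be conducted over 12 months, following regulatory approvals". The chart below has one row for training, one for the pilot (implementation together with follow-up) and one for analysis and the manuscript.

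Section 6.1 says "Participants will all be recruited and followed for 12 months". This can be read as 12 months for each person, or as 12 months for recruitment and follow-up together. Section 6.3, on feasibility of recruitment, says enrolment "is feasible in 3 months for a total of 105 ALWH in the entire study".

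Section 6.6 schedules the BDI-II and viral load at enrolment, month 6 and month 12. Section 6.7 has primary and secondary outcomes assessed at months 6 and 12 and sets viral suppression at month 12. Feasibility includes "the proportion of ALWH retained in each arm by the end of the study period".

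Section 10.0 pays travel for three study visits for each of 105 participants. Section 10.1 funds two research assistants at "100% effort for 12.0 months".

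**The concern.** A person enrolled at the end of a 3-month enrolment period reaches month 12 fifteen months after the first enrolment. The stated pilot window is 12 months, and the research assistants, who take consent under Section 7.6 and so are needed from the first enrolment, are funded for the same 12 months.

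If the pilot closed on a common date as written, late enrollees would have no 12-month viral load or BDI-II. Study retention is tied to the end of the study period and not to a visit, so it would cover a different length of follow-up for each person. Nothing in the protocol separates someone whose visit falls after closure from someone lost to follow-up. Sections 6.1 and 6.4 also describe clinics as allocated to arms. If that stands and clinics enrol at different speeds, follow-up length would differ by arm.

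**Working it through.** **Inputs**
- Project length 18 months; training in months 1 to 4; pilot 12 months (Section 9.0).
- Enrolment 3 months, N = 105, four clinics (Section 6.3).
- Last visit at month 12 (Sections 6.6 and 6.7).
- Assumption: enrolment is even over the enrolment period.

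**1. The plan's own calendar.** 18 − 4 − 12 = 2 months remain, presumably for analysis. The three durations fit 18 months only if the 12 pilot months already include enrolment.

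**2. Pilot window.** Needed: enrolment + follow-up = 3 + 12 = 15 months, against 12 stated.

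**3. Follow-up if the 12-month window is literal.** The first enrollee has 12 months and the last has 12 − 3 = 9; the median is 10.5. The share reaching month 12 is (window − 12) / enrolment period = (12 − 12) / 3 = 0, apart from anyone enrolled on day 1. The protocol text gives no window around the visit. With an assumed tolerance of 1 month early, the share is (13 − 12) / 3 = 33%, or 35 of 105.

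**4. Project window if training comes first.** The last 12-month visit falls at 4 + 3 + 12 = month 19, against 18, before any analysis.

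**5. Running visits to month 18 with no analysis time.** The window after training is 18 − 4 = 14 months. The share reaching month 12 is (14 − 12) / 3 = 67%, or 70 of 105. Keeping 1 month for analysis gives (13 − 12) / 3, or 35 of 105; keeping 2 months gives 0.

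**6. What would let all 105 reach month 12 by month 18.** Either enrolment starts by the end of month 3, overlapping training (3 + 3 + 12 = 18), or it finishes within 2 months of the end of training (4 + 2 + 12 = 18). Both leave no time for analysis.

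**7. Sensitivity to the enrolment rate.** Section 6.3 supports two rates.
- Its recruitment assumptions give 115 × 0.90 × 0.18 × 0.80 = 14.9 per clinic per month. Four clinics reach 105 in 105 / 59.6 = 1.8 months, so the last visit is at 4 + 1.8 + 12 = month 17.8. If a clinic must supply 35, it takes 35 / 14.9 = 2.3 months, and the last visit is at month 18.3.
- Its quoted rate of about 6 per clinic per month gives 6 × 4 × 3 = 72 in 3 months, not 105. Reaching 105 takes 105 / 24 = 4.4 months, so the last visit is at month 20.4 and 24 × 2 = 48 of 105 (46%) would have a 12-month visit by month 18.

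With either rate, enrolment plus 12 months of follow-up exceeds 12 months.

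**8. Month 6.** With 3 months of enrolment the last 6-month visit is 3 + 6 = 9 months after the first enrolment, and at the slower rate 4.4 + 6 = 10.4. Both fit within 12.

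**The case against.** The strongest reply is that no hard closure at 12 months is stated. The work plan calls the pilot both 18 and 12 months long, Section 6.1 can be read as 12 months per participant, and the budget pays three visits for all 105. The plan evidently intends everyone to have a 12-month visit, so the fault may be loose wording and not planned truncation. That stands as a reading of intent. It does not supply a calendar: with training first, 12 months per person still ends at month 19.

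The protocol also does not say that enrolment waits for training to end, and the shading of the work-plan chart cannot be read in the text available, so overlap is possible. That stands too, and month 19 is therefore conditional. The 15-against-12 comparison does not depend on it.

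The research-assistant months are weak evidence of when follow-up stops, because the budget is visibly partial: it has no line for counselors, peer supporters, the study nurse or viral load testing. They show that the 12-month figure recurs, not that visits end there.

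A reader might infer that 12-month outcomes cannot be observed for most participants. The documents do not support this in general. It follows if the 12-month window is a hard limit, but with visits to month 18 and the stated 3-month enrolment, 67% are observable. The 46% figure needs the rate of about 6 per clinic, which Section 6.3's own recruitment assumptions contradict. A reader might also infer that retention will be understated. That assumes closure would be counted as drop-out; the protocol does not say so, and a statistical analysis plan that is not shown may settle it.

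**Conclusion.** The durations contradict each other on the protocol's own figures. Three months of enrolment and a 12-month visit for everyone need at least 15 months; the pilot is given 12. Taken literally, follow-up is 9 to 12 months and 12-month outcomes are missing for nearly all participants.

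On the looser reading the size depends on the calendar. With training completed first, the last visit is at month 19. If visits run to month 18, about 70 of 105 have a 12-month visit. With overlap, or enrolment within about 2 months, all 105 can, at the price of any analysis time inside the 18 months. These counts assume even enrolment and no tolerance around the visit.

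The problem is confined to month 12 and to outcomes tied to the end of the study. Retention in care is defined by quarter and can be computed on shorter follow-up.

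**What to change.** Reconcile Sections 6.1, 6.3, 9.0 and 10 on one calendar that shows the enrolment period, 12 months of follow-up per participant, the date of the last visit and the time kept for analysis. Restate the pilot as enrolment plus 12 months (at least 15 months), say whether enrolment may overlap training, and move the project end date and research-assistant months to match. With 3 months of enrolment the extra salary is 2 × $450 × 3 = $2,700, plus $270 for the 10% committee fee. If enrolment is planned at about 6 per clinic per month, it is 2 × $450 × 4.4 = $3,960 before that fee.

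Define study retention as attendance at each participant's own 12-month visit, and count any closure before that visit as administrative, not as loss to follow-up. The BDI-II response outcome, which uses the same end point, should have the same anchor. This costs only wording.

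Making month 6 the common time point would fit a 12-month pilot, but it changes the viral suppression outcome that Section 6.7 sets at month 12. It is a change of endpoint for the sponsor to weigh, not a clarification.
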